### Study Outcomes and Measures

#### Overview

Table 3 presents the study outcomes and measures. All study participants will be asked to complete web-based questionnaires via REDCap at 3 time points: baseline (week 0), postintervention (week 8), and follow-up (week 20). In addition, participants will complete a weekly web-based sleep diary via REDCap from weeks 1 to 8 and at the end of week 20. Participants will also complete a weekly log via REDCap regarding their satisfaction with the study and whether there have been any changes in their cancer therapy, sleep medication and supplement use, and disease status. The weekly satisfaction logs will specifically include questions to assess the participants’ overall perceptions of their meditation or podcast sessions. If the participant meditates or listens to a podcast, they will be asked about their likes, dislikes, facilitators, and barriers. If they do not meditate or listen to a podcast, they will be asked what would help them.

**Table 3 table3:** Summary of data collection.

Data, outcomes, and measures				Week 1		Weekly		Week 8		Week 20

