	**Sleep medications**									
		Self-reported			✓				✓	

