
#### Analytic Approach

For preliminary analyses, univariate and bivariate statistics and plots will be used to examine the distributions of and associations between study variables, identify potential multivariate outliers and influential cases, explore patterns of missingness, and check for systematic between-arm differences in baseline participant characteristics. Before addressing the study aims, we will estimate multivariable linear regression models predicting week 8 and week 20 values of each outcome from the main effects of the treatment arm (arm) and the corresponding baseline value of the outcome (baseline) and an arm × baseline interaction term. If the interaction is not significant, an ANCOVA-type approach (described in the following paragraphs) will be used. However, if this interaction is significant, a generalized linear mixed model approach will be used, with repeated measurements of outcomes treated as nested within the participants. Preliminary analyses will inform the choice of link function (eg, natural log) and error distributions (eg, negative binomial) or the transformation of outcome scores used in the primary analyses. R (version 4.1.2) will be used for all analyses and plots.

To assess intervention effects on sleep quality and sleep-related impairment, we will use multivariable linear regression models (following an ANCOVA-type approach), predicting week 8 values on the ISI and secondary sleep outcomes, including the PROMIS Sleep Disturbance questionnaire and Sleep-related Impairment Scale, and sleep efficiency measured via sleep diaries and actigraphy from the study arm (Calm v podcast), adjusting for corresponding baseline values and relevant background covariates (eg, prestudy sleep medication dosage and BMI). These analyses, which will follow a strict intent-to-treat approach, will be supplemented by parallel analyses in which week 8 outcome values will be predicted from dose (minutes of meditation use), with the dose coded as 0 for the podcast arm, while adjusting for baseline outcome measure values and background covariates. These supplemental analyses will address heterogeneity in intervention exposure without including highly collinear arm and dose terms in the same models.

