All preliminary analyses will be supplemented by analyses exploring the interactions between biological sex (male vs female) and the focal effect in each model (eg, sex × arm in ANCOVAs or sex × arm × time in generalized linear mixed models) to determine whether these effects differ by sex. Furthermore, we will conduct sensitivity analyses by examining associations between time of day (eg, proportion of meditation bouts occurring within 2 hours of bedtime) and the proportion of sessions using nonmeditative content and outcomes at 8 and 20 weeks, adjusting for baseline outcome values. As these variables will be highly collinear with the study arm because podcast users will not have any recorded in-app meditation use, sensitivity analyses gauging the potential impact of these variables will parallel the dose-response analyses described previously. Further sensitivity analyses will be conducted to assess the potential impact of (1) changes in the chronic hematological cancer treatment regimen and (2) sleep disorder diagnoses that occur after randomization. For these, analyses of intervention effects will be repeated, excluding data from individuals who experience either of these events, and the results will be compared with those from the full intent-to-treat sample. To maintain the type I error rates at a nominal Cronbach α=.05, we will use *P* values adjusted using the Hommel approach [87].

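### Sensitivity analyses that drop everyone with a post-randomization event are no longer a randomized comparison and, as worded, also discard valid week-8 outcomes

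*Protocol article*

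**What the plan says.** All references are to the protocol article. For the main analyses, the Analytic Approach section states: "These analyses, which will follow a strict intent-to-treat approach". Later in that section, two further sensitivity analyses are set out. One concerns changes in the cancer treatment regimen, the other "sleep disorder diagnoses that occur after randomization". In both, the analyses of intervention effects are repeated "excluding data from individuals who experience either of these events", and "the results will be compared with those from the full intent-to-treat sample".

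On data collection, the Overview under Study Outcomes and Measures says that the weekly log asks about "any changes in their cancer therapy, sleep medication and supplement use, and disease status". Table 3 has rows for cancer therapy changes and for "Sleep medications", both self-reported weekly and at week 20. Neither the log description nor Table 3 names an item for a new sleep-disorder diagnosis. The ISI, the primary outcome, is scheduled in Table 3 at baseline, week 8 and week 20 only. The Missing Data section provides for multiple imputation with 100 data sets and allows auxiliary variables.

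**The concern.** A sensitivity analysis is useful when a difference from the main result has one clear meaning. Here the reader is meant to learn what regimen changes and new diagnoses do to the estimated effect. The rule selects participants by something that happens after randomization. A new sleep-disorder diagnosis is more likely in someone whose sleep stays poor, and a regimen change is more likely in someone whose disease is going badly. If the app works, fewer such people may be found in the Calm arm, so the rule would remove more of the poor outcomes from the control arm. A gap from intent-to-treat may then reflect this selection, the event itself, or both, and agreement may be accidental.

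There is also a problem of timing. The rule removes the individual and does not refer to when the outcome was measured. Read literally, a participant whose regimen changes in week 14 loses a week-8 ISI score that the event could not have touched.

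**Working it through.** **1. The plan's own sample size.** Inputs from Sample Size and Power: d = 0.45, pre-post correlation r = 0.30, significance level 0.05 (taken as two-sided), power 0.80. For a difference in change between arms:

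n per arm = 2 × (1.960 + 0.842)² × 2(1 − 0.30) / 0.45² = 2 × 7.85 × 1.4 / 0.2025 ≈ 108.5, so 109.

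The plan states 110 per arm, at which power by the t test is 0.80. Enrolment: 220 / 0.80 = 275, stated as 276. These figures reproduce.

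**2. What exclusion costs in precision.** The article gives no event rates, so these are assumptions. Excluding 10% or 20% of completers leaves 99 or 88 per arm, and power at d = 0.45 falls to 0.76 or 0.71. Setting values to missing also loses information, so this is a reason to read the re-run cautiously and not a gain claimed for the fix.

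**3. What exclusion does to the estimate.** Simulation with 400,000 participants per setting, analysed by ANCOVA. From the plan: ISI SD 6.0 and r = 0.30. Assumed: true effect 1.5 or 2.7 points (2.7 = 0.45 × 6), control event rate 10% or 20%, and event odds 2.0 or 2.7 times higher per SD of worse week-8 ISI. The simulated event has no effect of its own on the ISI, so any gap between the two estimates is selection alone.

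| Control event rate | Odds ratio per SD | Full sample | After exclusion | Gap |
|---|---|---|---|---|
| 10% | 2.0 | −1.505 | −1.455 | 0.050 |
| 10% | 2.7 | −1.503 | −1.422 | 0.081 |
| 10% | 2.0 | −2.693 | −2.609 | 0.084 |
| 10% | 2.7 | −2.698 | −2.527 | 0.171 |
| 20% | 2.0 | −1.512 | −1.433 | 0.079 |
| 20% | 2.7 | −1.495 | −1.349 | 0.146 |
| 20% | 2.0 | −2.676 | −2.515 | 0.161 |
| 20% | 2.7 | −2.707 | −2.465 | 0.242 |

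The effect shrinks by about 3% (0.084 / 2.693) to 10% (0.146 / 1.495). Loss is unequal, for example 20% of control against 14.5% of Calm participants.

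**4. Scale.** The ANCOVA standard error at 110 per arm is 6 × √(1 − 0.30²) × √(2/110) = 6 × 0.954 × 0.135 ≈ 0.77. The gap is therefore 0.050/0.77 = 0.06 to 0.242/0.77 = 0.31 standard errors.

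**5. Boundaries.** With a true difference of zero and 10% events in each arm, the bias is about 0. It reaches 0.22-0.75 points only under assumed gaps such as 15% against 5% or 25% against 10%, with odds ratios of 1.5 to 3. In those settings it runs against Calm because the control arm has more events. With more events in the Calm arm the sign would reverse.

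**6. Would imputation help?** Tested at the larger effect, with a pre-event diary variable in the imputation model:
- Events depend on the measured pre-event sleep: full sample −2.68, exclusion −2.59, imputation −2.68. The bias is removed.
- Events depend on the week-8 ISI itself: −2.71, −2.45, −2.50. Imputation recovers 0.05 of 0.26, about 20%. Across the settings tried the share was about 20%-45%.

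**The case against.** The strongest reply is that nothing rests on these analyses. Intent-to-treat is the main analysis, the exclusion is labelled a sensitivity analysis, and the two are to be compared openly. The bias is at most about a third of a standard error in the main settings, vanishes if events are alike in both arms, and depends on event rates and an ISI-event association that the article does not give. Eligibility makes events less likely: two months of stable therapy or observation is required, and planned drug changes and self-reported sleep-disordered breathing or movement disorders are excluded. A regimen change need not follow the ISI at all. Imputation is no complete cure either, because an event before week 8 removes the same ISI value that exclusion removes. All of this stands, and it limits the weight of the point. It does not make the excluded-sample contrast interpretable, and it does not justify discarding outcomes measured before the event.

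A reader might infer three stronger things that the document does not support:
- **That the primary result is biased.** It is not, since everyone is kept in the intent-to-treat analysis.
- **That sleep-disorder diagnoses are not collected, so the second analysis cannot be run.** The article is condensed and describes the log without reproducing its questions. The log's disease-status item might be stretched to cover a diagnosis. All that can be said is that no item is listed.
- **That sleep-medication starts are ignored.** They are logged, and intent-to-treat keeps those participants. No sensitivity analysis in the article addresses them, but adding one is an improvement and not the repair of an error.

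**Conclusion.** The point holds as a modest one about a rule that the article does state. Excluding people by post-randomization events gives a comparison that randomization no longer protects. Taken literally, it also discards week-8 scores that precede the event. A milder reading, in which exclusion applies only to outcomes after the event, is possible, but the wording does not say so.

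The likely size is 0.05-0.25 ISI points. This assumes control event rates of 10%-20%, event odds 2.0-2.7 times higher per SD of worse ISI, and a true effect of 1.5-2.7 points. It is near zero if events are equally frequent and alike in both arms. The conclusion that a gap from intent-to-treat could not be assigned to the event does not depend on these figures.

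**What to change.** Reword the two sensitivity analyses as follows.

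1. Keep all randomized participants and every outcome measured before the event. Set to missing only values measured after it.
2. Impute those values with the multiple imputation in the Missing Data section, adding baseline data and pre-event weekly diary and actigraphy data as auxiliary variables. For week-20 outcomes, a week-8 score that precedes the event also serves.
3. State that this assumes missingness at random given those data, and that it reduces but does not necessarily remove selection bias, because the ISI is measured only at baseline, week 8 and week 20.
4. As a low-cost addition, handle logged starts or changes of sleep medication or supplements in the same way.
5. Name the data source for new sleep-disorder diagnoses. If there is none, one item in the weekly log and the week-20 survey would supply it.

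The cost is a change of analysis wording, some programming and possibly one log item. The main analysis and sample size do not change. The downside is that the sensitivity result rests on the imputation model.

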#### Missing Data

If an ANCOVA-type approach is pursued, we will use multiple imputation to impute missing data by including all the variables from a given analytic model (ie, the variables with missingness will be included in the imputation model) in the imputation model, as well as potentially important auxiliary variables that are predictive of missingness or found to be associated with variables that have missingness [88]. With the *mice* package in R, we will use the fully conditional specification to generate 100 imputed data sets to be analyzed, as described previously [89]. Although generalized linear mixed models are robust to missingness in the response variable, data from participants with incomplete data on ≥1 covariate will be excluded from the analyses. Therefore, where warranted, we will use multiple imputation to generate imputed data sets to be analyzed via linear mixed models.

## Results

This project is funded by the NIH National Cancer Institute (R01CA262041). The projects kicked off in April 2022, and study recruitment is scheduled to begin in October 2022, with the total project duration lasting 5 years. We anticipate that we will be able to achieve our enrollment goal of 276 patients with chronic hematological cancer within the allotted project time frame.

## Discussion

### Principal Findings

The purpose of this study is to leverage an academic-industry partnership with the consumer-based app Calm to rigorously evaluate Calm for the effective delivery of a meditation intervention to patients with chronic hematological cancer via a 20-week RCT. Specifically, in this study, we aimed to (1) test the efficacy of daily meditation (≥10 minutes per day) delivered via Calm compared with a health education podcast control group on self-reported sleep disturbance, sleep impairment, and sleep efficiency; (2) test the efficacy of daily meditation (≥10 minutes per day) delivered via Calm compared with a health education podcast control group on inflammatory markers, fatigue, and emotional distress; and (3) explore the sustained effects at 20 weeks from the baseline of Calm in patients with chronic hematological cancer. This study will be the first RCT to determine the effects of a consumer-based mobile meditation app on sleep disturbances in patients with chronic hematological cancer. If our findings demonstrate a significant clinical impact on sleep disturbance in patients with chronic hematological cancer, we will have an inexpensive, easily accessible, nonpharmacological intervention that can readily be prescribed by cancer care providers for sleep disturbance in chronic hematological cancer. Our rigorous RCT will fill a knowledge and rigor gap regarding the delivery of smartphone-based meditation as an intervention for sleep and provide new data on sustained effects.

### Comparison With Prior Work

There is limited understanding of the effects of meditation on sleep-related outcomes in patients with cancer, with no research to date examining these outcomes in hematological cancers (1.9 million in the United States) [28,57]. Existing research using apps has focused on emotional measures or cancer-specific biological changes as outcomes but not sleep disturbance [90-94] in survivors of solid tumors with minimal residual disease or those with short survival times (eg, patients with metastatic solid tumors). The different and distinct long-term disease courses of patients with chronic hematological cancer and the associated maintenance therapy toxicities and symptoms warrant innovative interventions that support the self-management of symptoms [3]. Patients with chronic hematological cancer are often geographically dispersed, with substantial variability in their proximity to cancer centers because of the rarity of certain subtypes (eg, MPNs) [95], limiting opportunities for community-based local programs to help manage symptoms. Remote delivery of meditation via a mobile app will improve reach and scalability in this understudied population.

In addition, previous studies on meditation in cancer have focused primarily on White women with breast cancer [57]. This study presents an opportunity to study meditation in older adults, men, and minorities who present with chronic hematological cancer. Our prior successful recruitment strategies for patients with cancer will specifically recruit representative samples from these populations. Furthermore, we previously established that Calm is acceptable and appealing to a wide population group, which can expand the reach of traditional research interventions. For example, in a cross-sectional survey of Calm subscribers (N=12,151), 20% were male, 19% were people of color, and 15% were older adults (aged >65 years).

Prior studies using meditation to reduce sleep disturbance in patients with cancer did not have follow-up periods beyond 12 weeks [53]. In the 2 meditation-based interventions conducted in patients with chronic hematological cancer, both were delivered for a very short period (ie, 5 sessions of 1 hour per week). No product could be used continually and accessed beyond study completion [58,59]. As most evidence-based apps are developed within the context of research studies and are not sustained at the end of the study [96], the scalability and viability of the widespread distribution of mobile app–based interventions in these studies are not possible. As Calm is consumer based, the intervention never truly *ends*. Calm is available and can be used whenever a patient desires or feels it is needed (eg, when they feel overwhelmed, fatigued, anxious, or lying down to go to sleep). The patient can choose when and how frequently Calm is used, increasing the likelihood that patients will use Calm to alleviate sleep disturbance in the long term. This study can uniquely measure and explore time and dose effects and will advance the evidence for a consumer-based meditation app that patients with chronic hematological cancer can use for symptom self-management in the long term. This research will contribute to broader public health efforts by providing researchers and clinicians with an evidence-based commercial product to improve sleep in the long term in an underserved and understudied population with cancer and a high incidence of sleep disturbance.

### Future Directions

If it is demonstrated that Calm is an efficacious intervention for patients with chronic hematological cancer, future work will aim to disseminate Calm as an evidence-based option for health care providers to recommend or prescribe to patients with chronic hematological cancer. Consideration will be made to apply for a NIH Small Business Innovation Research grant to help with the dissemination of Calm or to receive Food and Drug Administration approval for Calm as a nonpharmacological intervention for the treatment of sleep in patients with chronic hematological cancer.

### Conclusions

In summary, this study will contribute to the mindfulness and cancer literature at large, with a unique focus on filling the much-needed gap by examining remote mindfulness-based interventions in patients with chronic hematological cancer.

## Abbreviations

ANCOVA: analysis of covariance
CBT-I: cognitive behavioral therapy for insomnia
CRP: C-reactive protein
CSD: Consensus Sleep Diary
IL: interleukin
ISI: Insomnia Severity Index
MBSR: mindfulness-based stress reduction
MPN: myeloproliferative neoplasm
NIH: National Institutes of Health
PROMIS: Patient-Reported Outcomes Measurement Information System
RCT: randomized controlled trial
REDCap: Research Electronic Data Capture
SDT: self-determination theory
TNF-α: tumor necrosis factor-α
